### Allocation, randomization and blinding

The eligible patients will be randomly allocated to their respective intervention group. The randomization schedule will be computer-generated and carried out by an investigator blinded to the recruitment, evaluation and treatment of the participants. Each patient’s allocation will be concealed using sequentially numbered, sealed and placed in opaque envelopes. The researcher that will provide the treatments who will be not involved in the data collection, will open the envelopes and will inform the group allocated to each participant. The participants will be informed if they would receive 1 out 2 different interventions to facilitate weight loss. Due to the nature of the interventions, it will not be possible to blind the physiotherapist that will provide the exercise training and the breathing and stretching programs; however, the nutritional and psychological interventions, as well as the assessments of each of the variables and the data analysis, will be given in a blinded manner.

### Interventions

#### Educational program

Both groups will complete an educational program consisting of 4 classes held twice a week before the interventions, each lasting 90 min. The 2 first classes will be based on an education videotape, the *ABC* of asthma, as well as presentations and group discussions pertaining to asthma pathophysiology, medication and peak flow meter skills, self-monitoring techniques, environmental control and avoidance strategies in accordance with previous studies [24, 36] and asthma guidelines [1]. During the 2 last classes, the patients will also receive information and educational materials regarding current international physical activity recommendations and the benefits thereof [35].

#### Nutritional intervention

A nutritionist will conduct the nutritional program with visits every 2 weeks during the 3 month intervention period, for a total of 6 sessions of 60 min each for both groups. The patients will be advised to follow a hypocaloric diet in which the calorie intake of each patient will be estimated by multiplying adjusted body weight (at a BMI of 25 kg/m^2^) by 20 calories [37]. Food consumption will be evaluated using a 24-h food record, and all caloric intake, macronutrients and micronutrients will be quantified using NutWin® software (recommended dietary allowances based on a food pyramid) [38]. The patients will complete the food dairy at the beginning (1^st^ session), the middle (3^rd^ session) and the end (6^th^ session) of the sessions. During each session, the nutritionist will measure and record the patients’ weights, discuss the importance of maintaining a balanced diet, and promote appropriate daily food intake and make each patient aware of the responsibility one bears in controlling one’s weight (Table 1).

**Table 1 Tab1:** Nutritional program

No. session	Activities
1	Presentation of the group and the nutritional program
	The measurement and recording of body weights, concepts of BMI/obesity range
	A balanced food pyramid and how to complete the 24 hour food intake dairy
2	The measurement and recording of body weight
	Individualized calorie goals with dietary suggestions
	Daily food routine and portion sizes
3	The measurement and recording of body weight
	The role of carbohydrates, proteins and fats in a diet
	Choices of low-energy and nutrient-dense meals and snacks
4	The measurement and recording of body weight
	The role of vitamins and minerals
	The ideal amount of nutrient intake to lose weight and stay healthy
5	The measurement and recording of body weight
	Healthy food preparation techniques and proposals for healthy meals
	The risk of diabetes and hypertension associated with obesity (comorbidities)
6	The measurement and recording of body weight
	“Virtual restaurant” and how to read a food nutrition labels
	Careful selection of restaurants and the finalization of the nutrition program

*BMI* body mass index, *No.* number of session. The nutritional program will be performed every 15 days over 3 months for a total of 6 sessions of 60 min each

#### Behavioural therapy

A psychologist will provide the therapy every 2 weeks for a total of 6 sessions of 60 min each for both groups. Group sessions using behavioural techniques (such as self-management, motivational strategies, positive reinforcement and relapse prevention) will be provided in order to improve patient adherence to the weight loss program [39]. The interventions will be based on the Transtheoretical model, which recognizes that behaviour changes are dynamic processes that move through stages and reinforces change via goal setting, skill development and self-control [39]. The psychologist will discuss several issues related to behaviour changes, using relaxation techniques, internal experiences and patient self-reporting (Table 2). The nutritional and psychological programs will be similar for both groups but they will be performed separately for each group to avoid that patients from distinctive groups meet themselves.

**Table 2 Tab2:** Psychological program

No. session	Activities
1	Presentation of the participants
	Explanation of the psychological program
	Assessment of patients’ expectations regarding weight loss
2	Breathing relaxation techniques to control anxiety
	Experiences concerning weight loss (successes and relapses)
	Identification of the reasons for and the onset of obesity in each patient
3	Emotional versus physiological hunger (learning to listen to the body)
	Feeding behaviour and pleasure from food
	The identification of personal barriers to weight loss and potential solutions to overcoming these barriers
4	Self-efficacy (dynamic group using drawings)
	A review of self-monitoring records and progress
	Realistic goal setting and action plans
5	Dynamic group called “time for self-care”
	Responsibility regarding food choices
	How to deal with relapses during the program
6	Dynamic group activities using the mirror to increase each patient’s morale
	A review of self-monitoring records and progress
	Finalization of the program

*No.* number of session. The psychological program will be completed every 15 days over 3 months for a total of 6 sessions of 60 min each

#### Exercise training program

The exercise training program will include aerobic and resistance exercises supervised by a physiotherapist and will be offered to only one of the groups (WL + E group). The program will be performed twice a week for 3 months for a total of 24 sessions of 60 min each. In order to avoid joint discomfort and improve patient adherence to the exercise program, aerobic training will be performed on both a treadmill (Jog 700, Technogym, Italy) and either a bike (Bike 700, Technogym, Italy) or an elliptical (Syncro 700, Technogym, Italy) machine. The intensity of the aerobic training will be based on peak oxygen consumption (peak VO_2_) and monitored using each patient’s target heart rate (THR). Exercise intensity will begin with a THR of 50 to 60 % of peak VO_2_ and will be increased by 5 % every 2 weeks based on symptoms and perceived exertion, using the modified Borg scales for leg discomfort and dyspnea [40], reaching a maximum of 75 % of peak VO_2_ [41]. Each patient will receive an accelerometer in order to record daily numbers of steps during the 1^st^, 6^th^ and 12^th^ weeks to encourage an increased physical activity level. In order to complete the amount of weekly physical activity recommended by the international guidelines [35], the patients will be also advised to walk at least twice a week for 30 min and to complete a daily physical activity record. Both heart rate and the modified Borg scale [40] will be assessed during each session before exercise, every 10 min during exercise and after exercise. Peak expiratory flow (PEF) will be measured before each session, and inhaled salbutamol (200 μg) will be recommended if values < 70 % were observed. The safety of the exercise training will be monitored by quantifying PEF, blood pressure and asthma symptoms before and after each exercise session as previously described [28].

The aerobic training will be interspersed with resistance training for the upper and lower limbs, targeting the following major muscle groups: chest, deltoid, quadriceps and hamstrings. Patients will begin the resistance training by performing 2 sets of 10 repetitions with an intensity of 50 % to 70 % of the one-maximal resistance test (1-RM) [42]; progression will take place first in the number of repetitions (until 2 sets of 15 repetitions are reached). When each patient reaches 15 repetitions, the load will be increased from 1 to 3 kg for the exercises for the upper limbs and 5 to 10 kg for the lower limbs, depending on the muscle being exercised and the patient’s tolerance level.

#### Sham treatment

The breathing and stretching exercise programs will be completed only by the WL + S group; the sessions will be performed twice a week for 12 weeks and will be supervised by a physiotherapist. The breathing and exercise programs will be performed as a sham treatment as previously described [24, 28], without an intensity progression. The program will be based on Yoga’s pranayama breathing exercises, including *kapalabhati*, *uddhiyana* and *agnisara,* as previously described [43]. Briefly, every exercise will be completed in 3 sets with 2 min of exercise intercalated with 60 s of rest for a total of 30 min each session. The stretching program will consist of exercises for the following major muscle groups: trapezius, pectoralis, gluteus, hamstrings, quadriceps femur, paraspinal, latissimus dorsi and pubic adductors. The exercises will be completed in 2 sets of 10 s each for a total of 30 min each session. The safety of these exercises will be monitored in the same way as the exercise training. The breathing and stretching exercises will be included as a sham intervention in the WL + S group in order to minimize the differences in the numbers of hospital visits and the amounts of patient attention between the two groups, not to induce respiratory breathing training benefits.

### Outcomes

#### Primary outcome

The primary outcome of this study will be the absolute change in the asthma control questionnaire (ACQ) post intervention between the groups following the intervention. The ACQ is both a reliable and validated method of measuring the impairment in asthma control [44, 45] and includes specific parameters regarding both daytime and nocturnal asthma symptoms, activity limitations, dyspnea, wheezing and rescue bronchodilator use within the last week (a short-acting B_2_-agonist) [45]. An additional question assessing forced expiratory volume in 1 s (FEV_1_) (% predicted, pre-bronchodilator) is completed by the researcher. The ACQ contains 7 items rated on a 7-point scale (0 = without limitation, 6 = maximum limitation), with a higher score indicating worse control. The ACQ has been validated for Brazilian Portuguese [46]. Previous studies have demonstrated that scores lower than 0.75 points are associated with good asthma control, whereas scores greater than 1.5 points are indicative of poorly controlled asthma [44]. A change of at least 0.5 points on the ACQ is regarded as clinically significant [47].

### Secondary outcomes

#### The asthma quality of life questionnaire (AQLQ)

The asthma quality of life questionnaire [48, 49] consists of 32 items rated on a 7-point scale (1 = great deal, 7 = not at all) divided into the following 4 domains: activity limitations, symptoms, emotional function and environmental stimuli. The AQLQ has been translated and validated for Portuguese patients [50]. A higher AQLQ score indicates a better quality of life; clinically effective treatment resulted in a 0.5 point increase in the score following the intervention [51].

#### Levels of anxiety and depression

Symptoms of anxiety and depression will be evaluated using the Hospital Anxiety and Depression Scale (HADS) [52], which consists of 14 items divided into 2 subscales (7 for anxiety and 7 for depression). Each item is scored from 0 to 3, with a maximum score of 21 points for each subscale. A score greater than 9 in each subscale suggests a diagnosis of either anxiety and/or depression [53].

#### Asthma symptoms and exacerbations

Asthma symptoms and exacerbations will be evaluated using a symptom diary as previously reported [24]. The asthma diary includes questions about episodes and symptoms (coughing, wheezing, shortness of breath, nocturnal awakenings and the number of puffs of as-needed β_2_-agonist). Days free of asthma symptoms will be considered when the patient did not report any symptoms; these days will be totalled on a monthly basis. Asthma exacerbations will be defined as an increase in symptoms associated with at least one of the following criteria: the use of ≥ 4 puffs of rescue medication per 24 h during a 48-h period, a need of systemic corticosteroids, an unscheduled medical appointment, and either a visit to an emergency room or a hospitalization.

#### Sleep disorders

The Berlin questionnaire will be used to estimate the risk (low to high) of obstructive sleep apnoea syndrome (OSA) [54]. The questionnaire consists of 10 items, divided into the following 3 domains: snoring and witnessed apnoeas (5 items), daytime sleepiness (4 items) and high blood pressure/obesity (1 item). Each category is classified as positive if the score is ≥ 2 points. Additionally, if the patients have at least 2 positive categories, they will be considered high risk for developing OSA. The Berlin questionnaire has been translated and validated for Portuguese [55]. The ActiSleep monitor (Pensacola, FL, USA) will be also used to objectively evaluate the sleep of patients. The participants will be instructed to use the monitor over a period of 7 consecutive nights on their non-dominant wrist. During this monitoring period, the participants will keep a sleep diary in which they will record the times at which they fall asleep, as well as when they awake each morning. We will analyze the following parameters: the total amount of sleep, sleep latency, the number and duration of awakenings and sleep efficiency [56].

#### Daily life physical activity (DLPA)

The accelerometer “ActiGraph GT3X” (ActiGraph, Pensacola, FL, USA) will quantify objectively the absolute change in DLPA. This device uses a solid-state tri-axial accelerometer to collect motion data on 3 axes (vertical and horizontals right-left and front-back) and measures and records time-varying accelerations [57]. The counts obtained in a given time period are linearly related to the intensity of the physical activity monitored during this period [58]. All units will be initialized via a computer interface to collect data in 60-s epochs in the 3 axes using specific software (ActiLife 6.9.5 Firmware version). Each participant will be instructed to use the accelerometer over a period of 7 consecutive days, with the device positioned securely on the patient’s hip (non-dominant side) using an elastic belt. During the study period using the accelerometer, the patients will keep a diary in which they will record bathing times and the times at which they begin to fall asleep and awake each morning. The accelerometer will record automatically each patient’s energy expenditure (Kcal), metabolic equivalent unit (MET), step counts, sedentary behaviour, and cut off points, as well as time (%) when sedentary or engaged in light, moderate or vigorous activity, and time (%) in the standing, sitting and supine positions [59].

#### Body composition

Body composition will be analyzed via an octopolar tactile bioelectrical impedance analysis (InBody720 - Biospace, Seoul, South Korea). An electrode system separately measures the impedance of the subject’s trunk, arms, and legs at 6 different frequencies (at 1, 5, 50, 250, 500 and 1000 kHz) and evaluates body segment. The equipment will analyze the percentages of body fat mass, soft lean mass, fat free mass, skeletal muscle mass and visceral fat area (cm^2^). The equipment has a high test-pretest reliability and accuracy [60]. The patients will be advised to fast for at least 4 h, refrain from physical activity for 8 h prior to testing, and avoid taking diuretics at least 24 h before testing [61].

#### Anthropometric indexes

The patients’ heights, weights (Filizola®, Brazil), waist circumferences, hip circumferences and waist to hip ratios (WHRs) will be measured using a standardized protocol [62, 63]. BMIs will be obtained by dividing patients’ weights in kilograms by their heights in meters squared (kg/m^2^) [64].

#### Cardiopulmonary exercise test (CPET)

The cardiopulmonary exercise test will be performed using an electrical cycle ergometer (Corival, Lode B.V.; Medical Technology, The Netherlands) linked to a digital equipped with an exercise evaluation system (CardioO_2_ System; Medical Graphics Corporation), in accordance with American Thoracic Society/American College of chest physicians (ATS/ACCP) guidelines [65]. Oxygen saturation (SpO_2_), as measured via pulse oximetry (Onyx, model 9500; Nonin, Plymouth, MN), and electrocardiography (Welch Allyn CardioPerfect, Inc., NY) will be monitored continuously during the tests. The following variables will be recorded breath-by-breath during rest, during exercise and following testing: work rate (WR), VO_2_, minute ventilation (VE), carbon dioxide production (VCO_2_), respiratory exchange rate (RER) and heart rate (HR). Additionally, blood pressure, the Borg score for leg discomfort and dyspnea, and inspiratory capacity (IC) will be measured at rest and every 2 min during testing until the end of testing [40]. The patients will perform a ramp-symptom-limited CPET consisting of 2 min of rest, 2 min of warm-up (unloaded pedalling) and an incremental work period (an increase from 10 to 20 W/min, taking into account the patient’s level of daily activity [66]. The predicted CPET values will be obtained from the Brazilian population [67].

#### Peripheral muscle strength

The maximal strength tests will be evaluated via a one repetition maximum test (1-RM) test in order to determine the load used at the beginning of resistance training [42]. The 1-RM test is defined as the maximum weight that an individual can lift in a single repetition and will be performed as previously described [42]. Briefly, the participants (1) will be familiarized with the equipment using minimal resistance; (2) will perform a 3-min warm-up period; (3) will complete 8 repetitions at approximately 50 % of the estimated 1-RM, followed by 3 repetitions of approximately 70 % of the estimated 1-RM; and (4) will complete single repetitions (maximum 5 trials) utilizing progressively heavier weights in order to meet the 1-RM. The recovery period among series should not be less than 1 min or more than 5 min. The 1-RM test will involve the following movements: extension of the arms, inclined bench press and seated leg press and extension of the feet.

### Evaluating possible mechanisms

#### Pulmonary function

Spirometry and lung volume measurements will be performed using a calibrated whole-body plethysmograph (Medical Graphics Corporation - MGC, St Paul, Mm, USA) according to both American Thoracic Society and European Respiratory Society (ATS/ERS) recommendations [68, 69]. Data related to IC, total lung capacity (TLC), expiratory reserve volume (ERV), functional residual capacity (FRC) and residual volume (RV) will be expressed both as totals and as percentages of predicted values [70]. A spirometer will be used to measure FEV_1_, forced vital capacity (FVC), forced expiratory flow 25–75 (FEF 25-75 %), peak expiratory flow (PEF) and maximal voluntary ventilation (MVV). Spirometry evaluations will be conducted before and after the administration of 200 mcg of inhaled salbutamol. Increases of either 12 % or 200 ml in FEV_1_ will be categorized as positive responses to bronchodilator therapy [68]. The predicted values will be provided by Pereira et al. [71].

#### Airway inflammation

Airway inflammation will be quantified using the exhaled fraction of nitric oxide (FeNO), using a portable analyser (NIOX MINO®; Aerocrine AB, Solna, Sweden), in accordance with ATS/ERS guidelines [72]. The patients will be asked to exhale fully while seated before inhaling through a NIOX filter until they will reach their total lung capacity, and immediately will exhale at a constant flow rate of 50 ml/s using a visual feedback system. The average levels of at least 3 acceptable measurements will be used. The patients will be instructed to avoid eating foods containing nitrate and caffeine and to avoid smoking and exercise 24 h before testing, as well as to refrain from ingesting either food or water for at least 2 h before testing. NO collection will be performed by the same professional at the same time of day in order to avoid changes in patients’ circadian rhythms. A cut off point of 25 parts per billion (ppb) will be used to either confirm or exclude a diagnosis of eosinophilic airway inflammation [72].

#### Systemic inflammation

Patients’ inflammatory systemic profiles will be assessed using blood-based markers. Venous blood samples will be collected following at least 8 h of overnight fasting, and the patients will be advised to avoid exercise, alcoholic and caffeinated beverages 24 h before testing. The cytometric bead array method (BD Biosciences, San Jose, CA, USA) will be used to analyse the levels of IL-1, IL-2, IL-4, IL-5, IL-6, IL-8, IL-10, IL-12, IL-13, TNF-α, vascular endothelial growth factor (VEGF), T-cell receptor beta (TGF-β) and the chemokines MIG/CXCL9, IP-10/CXCL10, IL-8/CXCL8, MCP-1/CCL2 and RANTES/CCL5. Serum leptin, adiponectin, CRP (ELISA, MILLIPORE), cortisol (Siemens, Immulite 200) and vitamin D (Ria-CT) levels will also be analyzed.

### Data analysis

#### Sample size

Sample size was calculated based on the minimal important difference of 0.5 points between the groups [47] on the ACQ questionnaire, with a standard deviation of 0.72 [73]. A sample size of 55 patients will be sufficient to detect an effect size of 0.5 between the 2 arms for 80 % alpha 2-sided, assuming up to a 20 % loss to follow-up.

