**Methods/Design:**

This is a randomized controlled trial with 2-arms parallel. Fifty-five moderate or severe asthmatics with grade II obesity (BMI ≥ 35 kg/m^2^) under optimized medication will be randomly assigned into either weight-loss program + sham (WL + S group) or weight-loss program + exercise (WL + E group). The weight loss program will be the same for both groups including nutrition and psychological therapies (every 15 days, total of 6 sessions, 60 min each). Exercise program will include aerobic and resistance muscle training while sham treatment will include a breathing and stretching program (both programs twice a week, 3 months, 60 min each session). The primary outcome variable will be asthma clinical control. Secondary outcomes include HRQL, levels of depression and anxiety, lung function, daily life physical activity, body composition, maximal aerobic capacity, strength muscle and sleep disorders. Potential mechanism (changes in lung mechanical and airway/systemic inflammation) will also be examined to explain the benefits in both groups.

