#### Statistical analysis

An intention-to-threat analysis will be used to preserve the effects of group allocation and provide an assessment of the practical impact of the treatment [74], as recommended by the CONSORT statement [75]. The normality of continuous outcomes will be assessed via the Kolmogorov-Smirnov test. Comparisons of the initial and final data will be analyzed via a two-way repeated-measures analysis of variance, and the categorical outcomes, via the *χ*^2^ test. A partial correlation will be used to test the effects of airway and systemic inflammation as mediators. P values ≤ 0.05 will be considered statistically significant. The statistical analysis will be blinded to the treatment allocation and will be performed using specific software (SigmaStat 3.5, Systat Software Inc.).

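### On the plan's own inputs, 55 patients with 20 % loss give about 61 % power for 0.5 ACQ points, not 80 %; the statement also labels 80 % as alpha and a difference in points as an effect size

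*Protocol article*

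**What the plan says.** The Sample size section of the protocol article gives the target: "Sample size was calculated based on the minimal important difference of 0.5 points between the groups", on the ACQ, "with a standard deviation of 0.72". It then concludes: "A sample size of 55 patients will be sufficient to detect an effect size of 0.5 between the 2 arms". The operating characteristics are given as "for 80 % alpha 2-sided", and attrition as "assuming up to a 20 % loss to follow-up". The word power does not appear, and no significance level is given there. The level comes from the Statistical analysis section: "P values ≤ 0.05 will be considered statistically significant".

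The abstract shows that 55 is the total over both arms, not the number per arm: "Fifty-five moderate or severe asthmatics with grade II obesity" are to be randomised, and "This is a randomized controlled trial with 2-arms parallel".

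The primary outcome is the between-group comparison of the absolute change in ACQ. The planned analysis is a two-way repeated-measures analysis of variance.

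**The concern.** The paragraph supplies nearly all the inputs for a standard two-sample calculation, and the result can be checked. An SD of 0.72 and a difference of 0.5 points call for more than 60 evaluable patients at conventional error rates, so a total of 55 that also absorbs 20 % loss looks too small.

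Two labels make the statement harder to trust. An alpha of 80 % is not a usable significance level and conflicts with the 0.05 threshold, so the 80 % can only sensibly be power. An effect size of 0.5 normally means half a standard deviation, whereas the preceding sentence gives 0.5 in ACQ points.

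This is the only justification of the trial's size, and it concerns the primary outcome. If power is near 61 %, a true benefit equal to the minimal important difference would be missed about 4 times in 10. Readers would then weigh a null result against 80 % power that the design does not have.

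**Working it through.** **Inputs**

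- Difference: 0.5 ACQ points (Sample size).
- SD: 0.72 (Sample size). Taken first as the SD of the analysed quantity, the change in ACQ.
- Power: 80 % (Sample size, where it is labelled alpha).
- Significance level: two-sided 0.05 (sidedness from Sample size, level from Statistical analysis).
- Loss: up to 20 % (Sample size).
- Total: 55 (Sample size and abstract).
- Allocation: 1:1, an assumption, since the ratio is not stated.

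With two time points, the group-by-time test in a repeated-measures ANOVA is equivalent to a two-sample t-test on change scores, so the usual two-means formula applies.

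**Number needed**

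Standardised difference: d = 0.5 / 0.72 = 0.694.

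Normal approximation: n per arm = 2 × ((1.960 + 0.842) / 0.694)² = 32.6, so 33 per arm and 66 in total. The noncentral t gives 33.5, so 34 per arm and 68 in total.

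After 20 % loss: 66 / 0.8 = 82.5, so 83; 68 / 0.8 = 85. Inflating by 1.2 instead still gives 80 to 82. None of these is near 55.

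**What 55 delivers**

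Evaluable after 20 % loss: 55 × 0.8 = 44, or 22 per arm.

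| Evaluable | Power for 0.5 points (t) | Power (normal approx.) | Difference detectable at 80 % (t) |
|---|---|---|---|
| 44 (22 + 22) | 61.4 % | 63.4 % | 0.62 points |
| 55 (27 + 28) | 71.5 % | 73.1 % | 0.55 points |

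For 22 per arm to give 80 % power at 0.5 points, the SD would have to be about 0.58 rather than 0.72.

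**Attempts to reproduce 55**

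- One-sided 5 % with no allowance for loss: 26.3, so 27 per arm and 54 in total. Close, but it contradicts both the two-sided test and the loss allowance. With loss it becomes 65 to 68.
- 90 % power, two-sided (normal approximation): 44 per arm, and 44 / 0.8 = 55 per arm. This contradicts the 80 % and the total of 55 (it would be 110).
- Two-sided alpha of 20 %: 38 evaluable, 48 with loss. No match.
- Effect size of 0.5 read as standardised: 64 per arm (63 by normal approximation). Power would be 37 % with 44 evaluable and 44 % with 55. The preceding sentence of the plan argues against this reading; it is shown only to indicate what the wording would imply.

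**If 0.72 is the SD of a single score**

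The SD of the change is then 0.72 × √(2(1 − ρ)), where ρ is the correlation between baseline and final ACQ. The plan gives no ρ, so this is a range (44 evaluable, t-test on change):

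| ρ | 0 | 0.4 | 0.5 | 0.6 | 0.7 |
|---|---|---|---|---|---|
| Power | 36 % | 54 % | 61 % | 71 % | 83 % |

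Power reaches 80 % where the SD of the change falls to 0.578: 1 − (0.578 / 0.72)² / 2 = 0.68.

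**The case against.** The strongest counter-argument concerns the SD. The plan does not say whether 0.72 belongs to a single ACQ score or to its change. If it is a single-score SD and the baseline-final correlation is about 0.68, then 44 evaluable patients do give 80 % power with a two-sided test and 20 % loss, and 55 is consistent. So 61 % is conditional, not a fixed property of the design. That stands as a caveat, but it does not support the stated number: no correlation is given or used in the calculation, and any correlation below 0.5 puts power under 61 %.

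Second, the loss is an upper limit, so 44 is the floor. With the SD taken as that of the change, power runs from 61 % at 20 % loss to 71 % at none, and a true 0.5-point benefit would be missed between about 4 and 3 times in 10. This is fair, but even the favourable end falls short of 80 %.

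Third, the plan never literally claims 80 % power, and the allocation ratio is assumed. Both are true. No other sensible meaning of the 80 % is available, given the 0.05 threshold.

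Fourth, more than one route leads to the number 55, so it cannot be said how it arose. Agreed; the conclusion does not depend on its origin.

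**Conclusion.** The concern holds. From the stated inputs (0.5 points, SD 0.72, two-sided 5 %, 80 % power, up to 20 % loss) the trial would need about 83 to 85 randomised patients, some 30 more than the 55 planned. As planned, power for 0.5 points is about 61 % at the budgeted loss and about 71 % with complete follow-up. The difference detectable with 80 % power is 0.62 or 0.55 points respectively, both above the minimal important difference that the plan names as its target.

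The power figures rest on 1:1 allocation and on 0.72 being the SD of the change in ACQ. That the stated inputs do not lead to 55 is certain. The exact power is less so, because it would move with the baseline-final correlation if 0.72 is a single-score SD. The mislabelling of power as alpha, and of points as effect size, is plain on the page. Since this is the sole sample-size justification for the primary outcome, it must be corrected.

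**What to change.** Rewrite the Sample size paragraph; enrolment can stay at 55.

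1. Say whether 0.72 is the SD of the ACQ score or of its change, and state the 1:1 ratio if that is intended.
2. Name the 80 % as power and give alpha as two-sided 5 %.
3. Express the target as 0.5 ACQ points instead of an effect size of 0.5.
4. State what the design delivers. If 0.72 is the SD of the change: 55 randomised, 44 evaluable after 20 % loss, about 61 % power for 0.5 points, or 80 % power for 0.62 points. If it is a single-score SD: give the assumed baseline-final correlation with its basis, and recompute.
5. If the primary analysis becomes baseline-adjusted, restate power on that basis with the same correlation.

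The cost is one paragraph and a less favourable stated power. No extra patients are needed, and neither the primary test nor the type I error changes.
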